**Fig. 5 Fig5:**
[figure not shown]
Corresponding analysis groups

### Assessment of differences in asthma control between the intervention group and the usual care group in the percentage of well controlled asthma-like symptoms after 1- and 2-year follow-up.

The effect of the intervention on asthma control will be assessed by comparing the outcome measures between the intervention and the usual care group in the RCT. Asthma control will be scored using the validated TRACK questionnaire. Differences of the continuous outcome measure between the intervention group and the usual care group will be tested for significance with the unpaired t-test for normally distributed parameters and the Mann Whitney-U test in case of a not-normal distribution.

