### Outcomes

#### Randomised controlled trial

Primary outcome: difference between the intervention group and the usual care group in the percentage of well controlled asthma-like symptoms after 1- and 2-year follow-up. The percentage well controlled asthma-like symptoms will be based on the validated TRACK questionnaire.Secondary outcomes: differences after one year and at the end of the study between the intervention group and usual care group will be assessed with respect to:Number of exacerbationsLung function (spirometry) at 6 years of ageAirway resistance with forced oscillation techniqueQuality of life of children and their parentsPharmacotherapy (frequency and dosage of used medication)Growth velocity over 12, 24 and 36 months (cm/y), change in height SD scores over 12, 24 and 36 monthsPatient reported side-effects of medicationHealthcare resource use and –costs (standard and extra clinical visits, hospital admissions, referrals, laboratory tests, imaging tests)Costs outside healthcare (over-the-counter drugs)Absence of school and work (parents);

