### Sample size

*Randomised controlled trial* With a presumed percentage of well-controlled preschool children with asthma-like symptoms of 20% in the usual care group (based on reference [32, 33]), and of 40% in the intervention group, 91 patients in both groups are needed to detect this difference with an alpha of 0.05 and a power of 80%. Taking a dropout rate of 10% into account, we aim to include a total number of 220 preschool children with asthma-like symptoms.

*Prospective cohort study* For studies assessing the relationship between microbiome, transcriptomics, epigenetics, and atopic outcomes like asthma, a sample size of 70–80 is considered adequate [34, 35].

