### Questionnaires

Parents will be asked to complete several questionnaires during the study to assess asthma control, quality of life, and utilisation of health care and societal resources [40–42]. The questionnaires will be provided as e-version and will be sent to the parents two weeks before the annual clinical visits. Two questionnaires will be sent at a three-monthly interval: the questionnaires on asthma control (TRACK) and on utilisation of health care and societal resources.

*TRACK* Parents will be asked to complete the TRACK questionnaire at a 3-month interval. The TRACK questionnaire is a validated questionnaire on asthma control specifically developed for use in this age group, independent of the diagnosis. A score of 80 or more is defined as well controlled disease. The TRACK score is sensitive and reliable, and an increase of 10 points was found to be the ‘minimally important difference’ [43].

*ISAAC questionnaire (Core Questionnaire and Environmental Questionnaire)* The Core Questionnaire and the Environmental Questionnaire have been developed by the ISAAC steering Committee [44]. This questionnaire is used in this study to assess asthma, allergic rhinoconjunctivitis and eczema in all participants and to assess a variety of environmental factors.

*EQ-5D-Y (proxy version)* The EQ-5D-Y questionnaire is a validated child-friendly version of the EQ-5D on quality of life that comprises the following five dimensions with three answer levels (“no problems,” “some problems,” and “a lot of problems”): mobility, looking after myself, doing usual activities, having pain or discomfort and feeling worried, sad or unhappy. It also includes a visual analogue scale (VAS), which gives an overall assessment of the child’s health status in a scale from 0 (worst imaginable health state) to 100 (best imaginable health state). In the proxy version, the caregiver is asked to rate the child’s health-related quality of life (HRQoL). The EQ-5D-Y proxy-version has been tested in children as from 4 years of age [45], which revealed that some domains (e.g. self-care) were sometimes perceived by the parents as not suitable to young children. However, no alternative preference-based measure is currently available or has a validated proxy-version for use in preschool children.

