**Randomised Controlled Trial**			
*Primary*			
Difference in the percentage of well controlled asthma-like symptoms after 1-year follow-up	I	TRACK-score	Unpaired t-test / Mann Whitney-U test
*Secondary*			
Pharmacotherapy	I, II, III, IV	Cumulative ICS dosage (fluticasone equivalent)	Mann Whitney-U test
Growth retardation	I, II, III, IV	SD deviation from target height	Unpaired t-test
Amount of exacerbations	I, II, III, IV	Amount	Chi-square test
Amount of hospital admissions	I, II, III, IV	Amount	Chi-square test
Quality of life child	I, II, III, IV	EQ-5-DY by proxy	Unpaired t-test / Mann Whitney-U test
Quality of life caretaker	I, II, III, IV	EQ-5-DY	Unpaired t-test / Mann Whitney-U test
Lung function (tremoflo)	I, II, III, IV	R_5_, R_5-20_, X_5_, X_5-20_, AX, F_res_ (baseline and % change after salbutamol)	Unpaired t-test / Mann Whitney-U test
Lung function (spirometry)	II, III, IV	FEV_1,_ FVC, MEF50 (baseline and % of change after salbutamol)	Unpaired t-test / Mann Whitney-U test
Absence of school and work (parents)	I, II, III, IV	Number of days	Chi-square test
Healthcare resource use and –costs	I, II, III, IV		Unpaired t-test / Mann Whitney-U test
Costs outside healthcare	I, II, III, IV	Euro	Unpaired t-test / Mann Whitney-U test
Cost-effectiveness	I, II, III, IV	Societal cost per QALY and health care cost per additional child with control of asthma-like symptoms	Sensitivity and bootstrap analysis

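### The primary outcome and sample size are for a percentage well controlled, but the only primary test named compares the continuous TRACK score

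*Protocol article*

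**What the plan says.** Three places in the protocol article describe a binary endpoint.

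- Outcomes, Randomised controlled trial: the primary outcome is the "difference between the intervention group and the usual care group in the percentage of well controlled asthma-like symptoms after 1- and 2-year follow-up". It adds: "The percentage well controlled asthma-like symptoms will be based on the validated TRACK questionnaire".
- Questionnaires, TRACK: "A score of 80 or more is defined as well controlled disease".
- Sample size: "With a presumed percentage of well-controlled preschool children with asthma-like symptoms of 20% in the usual care group" "and of 40% in the intervention group", for which "91 patients in both groups are needed to detect this difference with an alpha of 0.05 and a power of 80" per cent.

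Two places describe a continuous analysis of that endpoint.

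- The statistical section on differences in asthma control, whose heading names the percentage well controlled, says: "Differences of the continuous outcome measure between the intervention group and the usual care group will be tested for significance with the unpaired t-test". Mann-Whitney U replaces the t-test if the distribution is not normal.
- The primary row of Table 2 lists "Difference in the percentage of well controlled asthma-like symptoms after 1-year follow-up", gives the TRACK score as outcome measure, and names the unpaired t-test or Mann-Whitney U test as method.

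The next statistical section, on health gain and costs, assigns chi-square to dichotomous parameters. It later refers the reader to Table 2 for the method used for each outcome. The primary row of that table contains no test of proportions.

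**The concern.** A t-test concerns a difference in mean score, and a Mann-Whitney test concerns ranks. Neither estimates or tests a difference in the percentage above a cut-off.

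The two questions can have different answers. If poorly controlled children improve but stay below 80, the score comparison can be positive with no gain in the percentage controlled. If the gain is concentrated among children just under 80, the percentage can rise substantially while the mean moves little.

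Two things are at stake. First, the trial could report its primary outcome as met, or not met, on a quantity other than the one it declared. Second, the power statement describes a test other than the one named for the primary outcome.

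**Working it through.** **Inputs from the article.** 20% and 40% well controlled, alpha 0.05, power 80%, 91 per arm (Sample size); two-sided testing (Statistical methods); cut-off 80 and minimally important difference 10 points (TRACK paragraph). The article gives no TRACK standard deviation and no target mean difference, so both are assumptions below.

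**1. Reproduce the 91.** Pooled proportion 0.30, difference 0.20.

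- Without continuity correction: n = [1.960·√(2·0.30·0.70) + 0.842·√(0.20·0.80 + 0.40·0.60)]² / 0.20² = (1.2702 + 0.5323)² / 0.04 = 81.2.
- With continuity correction: n = (81.2/4)·[1 + √(1 + 4/(81.2·0.20))]² = 90.9, rounded up to **91**.

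The stated figure is therefore a two-sided, continuity-corrected two-proportion sample size.

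**2. Power of the named test if 20% versus 40% comes from a pure shift.** Assume normal scores with equal SD in both arms.

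- Standardised shift: d = z(0.80) − z(0.60) = 0.842 − 0.253 = 0.588.
- Power at 91 per arm: Φ(0.588·√(91/2) − 1.960) = Φ(2.008) = about **98%** for the t-test, and about 97% for Mann-Whitney.

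**3. Power of the named test for the 10-point important difference.** Power = Φ((10/SD)·√(91/2) − 1.960).

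| Assumed SD | Power at 91 per arm |
|---|---|
| 15 | 99% |
| 20 | 92% |
| 25 | 77% |
| 30 | 61% |

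Power falls below 80% once the SD exceeds 10 / [(1.960 + 0.842)·√(2/91)] = about 24.

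**4. A case where the two questions part.** This is a constructed illustration, not a forecast. Control scores are normal with SD 20 and 20% at or above 80. In the intervention arm, only children within about 12 points below 80 gain, by just enough to cross. The percentages are then 20% and 40%, but the simulated means are 63.2 and 65.6. Over 3,000 simulated trials with 91 per arm, the t-test and Mann-Whitney test each had about 12% power, and the chi-square test about 85%.

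**5. Power of a test of proportions at the planned size.**

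- 91 per arm: Φ[(0.20 − 1.960·√(2·0.21/91)) / √(0.40/91)] = about **84%** by uncorrected chi-square; **81%** by Fisher's exact test (exact enumeration).
- 99 per arm (110 less 10%): about 87% and 84%.

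The planned size supports the binary test as it stands.

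**The case against.** The strongest reply is that the plan already contains the right test: dichotomous parameters go to chi-square, and the Discussion describes health gain as a higher proportion of children with asthma control. On that view a chi-square test of the controlled proportion lies within the plan. This stands in part: it would be wrong to infer that the proportion will never be tested. It does not remove the contradiction. The chi-square sentence sits under a different heading, the primary outcome has its own section naming only the continuous tests, and Table 2 repeats them. Other rows of the table do name chi-square, so it cannot be read into the primary row by default. Nor can this be left to an unseen analysis plan, because the article states a specific test that conflicts with its own endpoint.

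Three stronger readings are tempting but unsupported.

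- *The trial is underpowered.* A reader might infer this from the mismatch. Under the simplest assumption the named test has more than 80% power; under others it has less. The documents do not settle which.
- *The t-test lowers the bar to less than half the planned effect.* Under the normal-shift assumption it reaches p = 0.05 at d = 0.29, about 29% versus 20%. The fair benchmark is not the planned 20 points. With 91 per arm the chi-square test is itself significant at 18 versus 30 children controlled (13.2 points, p = 0.044 uncorrected) or 18 versus 31 (14.3 points, p = 0.045 corrected). The contrast is about 9 points against 13 to 14.
- *The cost per additional controlled child rests on an untested effect.* That ratio uses the proportion directly, and its uncertainty is handled by bootstrap and sensitivity analysis, whichever primary test is run.

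Choosing between t-test and Mann-Whitney from the observed distribution is a lesser matter. The same wording covers most continuous outcomes, and an article may leave the detail to a fuller plan.

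**Conclusion.** The concern holds as an internal contradiction: the stated primary test does not test the stated primary outcome. This follows from the text alone and needs no distributional assumption.

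The 80% power is correct for a two-proportion test and does not apply to the test named. The latter's power cannot be derived from the article. The illustrative range is about 98% under an equal-variance normal shift, and 99% down to 61% for a 10-point difference with SD 15 to 30. It is lower still if the benefit is confined to children near the cut-off. All these figures rest on assumed distributions. The sample size is not in error.

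The contradiction should be resolved before any analysis by arm, since otherwise a comparison of proportions and a comparison of scores could each be presented as the planned primary analysis.

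**What to change.** In the section on differences in asthma control and in the primary row of Table 2, name the comparison of the proportion with TRACK of 80 or more as the primary analysis. Report a risk difference with 95% confidence interval and a chi-square test, or a logistic model with a standardised risk difference. Keep the continuous TRACK score as a named secondary analysis with one method fixed in advance, read against the 10-point important difference.

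Redefining the primary outcome as the mean TRACK score would also reconcile the text, but it would need a stated SD, target difference and new power calculation. It would also depart from the endpoint on which the trial was sized, so the first route is preferable.

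The cost is wording in one section and one table row, with no new data and no extra patients.

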### Assessment of improvement in health gain and costs of care with the application of the breath test in wheezing preschool children

The effect of the intervention will be assessed by comparing the outcome measures between the intervention and the usual care group in the RCT. Dichotomous parameters will be tested with the chi-square test. Continuous variables will be tested for significance with the unpaired t-test for normally distributed parameters and the Mann Whitney-U test in case of a not-normal distribution.

Total treatment costs will be calculated by multiplying resource use with the costs per unit. Resource use (visits to the general practitioner or specialist, emergency visits, hospital admission, lung function tests and other diagnostic procedures, the breath test, (over-the-counter) medication, and lost work days by parents due to sickness of the child) will be obtained from a specially designed questionnaire with a recall period of three months. The parents will fill out this questionnaire at baseline and at 3 months interval during the follow-up. Sources for valuation of the costs will be cost-prices of the Dutch manual for costing and cost-prices from the Dutch pharmacotherapeutic compass [45, 47–49] (reference data 2022). If necessary, local hospital cost-prices will be used, which are largely based on integral cost-prices from the Dutch hospitals [50]. Absence of work reported by the parents will be calculated by using the friction cost method, which is recommended by the Dutch manual for costing [47, 48].

The cost-effectiveness analysis from the healthcare perspective will be based on symptom control according to the TRACK questionnaire at 1 year follow-up (primary outcome measure). The cost-effectiveness analysis from the societal perspective will be based on the EQ-5D-Y. The EQ-5D-Y will be completed at baseline and at 3 months intervals during the follow-up, and will be filled out by one of the parents.

A cost-effectiveness analysis will be performed from a societal and healthcare perspective with a time horizon of 2 years. Incremental cost-effectiveness ratios will be calculated as societal cost per QALY (societal perspective) and health care cost per additional child with control of asthma-like symptoms (healthcare perspective). Standard sensitivity- and bootstrap analysis will be performed to address uncertainty regarding costs and cost-effectiveness outcomes. Cost-effectiveness acceptability curves will be constructed reflecting the probability that the diagnostic breath test is cost-effective for a range of threshold values. Costs and effects after one year will be discounted at 4.0% and 1.5% respectively, according to the Dutch guidelines for health economic evaluation [45, 48].

All outcome parameters and corresponding outcome measures and methods of analysis are listed in Table 2. The large number of patients (*n* = 220) allows better representation of specific subgroups of specific age, background (primary or secondary/tertiary care), genetic predisposition, and geographic area. All these parameters will be measured and included in the multivariable analysis in order to assess possible influences on outcome. Intention-to-treat analyses will be applied. We will execute two subgroup analyses: one for age and one for level of care (first-line versus secondary/tertiary care). Two-sided *p*-values < 0.05 (with correction for multiple testing) will be regarded as statistical significant.

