### Intervention

The intervention in the RCT consists of providing a probability diagnosis of either asthma or transient wheeze based on the earlier developed breath test of the ADEM study [22]. Based on this probability diagnosis, disease-specific recommendations on treatment and follow-up will be provided to the parents and treating physicians. At the start of the study, exhaled breath will be collected and sent to the central laboratory in the Maastricht UMC + for analysis on a GC-*tof*–MS. After analysis, the chromatogram is compared with our central database (based on the results of the ADEM study [22]) in order to determine whether the newly taken breath sample fits an asthmatic or a transient wheeze pattern of the selected VOCs. Parents and doctors of children allocated to the intervention group will receive the test result (probability diagnosis “asthma” or “transient wheeze”) within three months after the start of the study. In the children with a test result of “transient wheeze” in the intervention group, a restrictive policy towards use of asthma medication and referral to specialist care will be advised. In children with a test result of “asthma”, treatment with asthma medication according to international guidelines will be advised [29]. Parents and doctors of patients allocated to the usual care group will receive the test result at the end of the study at the age of 6 years. The management of preschool children with recurrent wheezing will be in accordance with national and international guidelines [29–31]. Both in the intervention and control group, treating doctors are at any time free to prescribe asthma medication, antibiotics or other drugs they judge as clinically necessary or meaningful.

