### Participant timeline

Both wheezing participants and healthy participants follow the same timeline (Fig. 1). Participants enrol in the study, after informed consent, at the age of 2 or 3 years old. At the baseline visit, the wheezing children that participate in the RCT will be randomised into either the intervention group or the usual care group. All children included in the study will perform the study-related procedures, including the breath test, at the baseline visit (see section “data collection” and Fig. 2). The children that will be allocated to the intervention arm of the RCT will receive their probability diagnosis and corresponding treatment advice within three months of the baseline visit. All children will be invited for the annual, study-related hospital visits until the age of 6. The performed study procedures at each visit are illustrated in Fig. 2. All parents will receive online questionnaires prior to the annual visit (a list of the questionnaires is provided in Fig. 3). Parents of children that participate in the RCT will also receive questionnaires on disease control and healthcare related expenditures with a 3-month interval. At the age of 6, a final diagnosis will be made based on respiratory symptoms, use of medication, and objective lung function measurements as reported previously [22].

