### Methodological issues

We decided to choose a RCT design for the following reasons: 1) to assess the full potential of the breath test in health gain and costs of care, a comparative study design is needed; 2) the breath test is not standard care yet; 3) in the usual care group, it is not unethical to provide the test result in a later phase, eventually all children/parents will benefit from the breath test result; 4) a safety rule will be applied in the usual care group so that parents/treating doctors can get the result of the breath test in an urgent situation (e.g. severe exacerbations, hospital admissions).

At first, we did not expect any problems with the feasibility of patient recruitment based on the high prevalence of children with asthma-like symptoms and our experiences during the first ADEM study. However, the outbreak of the SARS-CoV-2 pandemic in 2020 significantly affected the recruitment of participants. In the beginning of the pandemic, we were not allowed to perform research anymore by the Board of Directors of our hospitals. In a later phase, less preschool children with wheezing symptoms presented themselves at the outpatient clinic, emergency departments, and primary care facilities than before the crisis, which probably was the consequence of preventive measures taken (e.g. the lock-downs and temporary closure of schools and day-care facilities). As most of our patients were selected during and after the pandemic, this influenced intervention and control group equally.

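### The breath test's own cost is to be counted from parental recall although both arms have the test, so part or all of it may drop out of the incremental cost

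*Protocol article*

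**What the plan says.** All references are to the Protocol article.

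- **Costing rule** (*Assessment of improvement in health gain and costs of care*): "Total treatment costs will be calculated by multiplying resource use with the costs per unit".
- **Source of the quantities** (same section): the resource list includes "lung function tests and other diagnostic procedures, the breath test, (over-the-counter) medication", and the listed quantities "will be obtained from a specially designed questionnaire with a recall period of three months". On timing: "The parents will fill out this questionnaire at baseline and at 3 months interval during the follow-up".
- **Who has the test** (*Participant timeline*): "All children included in the study will perform the study-related procedures, including the breath test, at the baseline visit".
- **What separates the arms** (*Intervention*): "The intervention in the RCT consists of providing a probability diagnosis of either asthma or transient wheeze". For the comparator: "Parents and doctors of patients allocated to the usual care group will receive the test result at the end of the study", that is, at age 6.
- **Exception for urgent cases** (*Methodological issues*): "a safety rule will be applied in the usual care group so that parents/treating doctors can get the result of the breath test".
- **Questionnaire content** (*Questionnaires*, utilisation of health care and societal resources): visits, admissions, lung function and other diagnostic procedures, and medication are described. The breath test is not named.

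The paragraphs that follow the costing rule define two ratios over a 2-year horizon, societal cost per QALY and health-care cost per additional child with controlled symptoms. They also promise acceptability curves for whether the breath test is cost-effective.

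**The concern.** The strategy under evaluation is testing plus disclosure. The cost that certainly separates it from usual care is one test per intervention child. The plan obtains that quantity from a source that cannot tell the arms apart reliably. Parents in both arms saw their child take the test, and the questionnaire as described has no item for it. What enters the cost difference is then a difference in reporting behaviour, not a difference in strategy.

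The primary objective is to show health gain together with lower costs, and the article itself calls the GC-based test expensive. A count that omits some or all of the test's cost moves the incremental cost in the direction the trial hopes to find. Bootstrapping does not repair this, because each resample draws from the same recorded costs. The sensitivity analysis is described only as standard and is not said to vary how the test is charged.

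**Working it through.** **Reproducing the plan's figure.** The only stated figure that bears on the size is the planned effect in *Sample size*: 20% v 40% well controlled, 91 per group, alpha 0.05, power 80%. The two-sided normal-approximation formula for two proportions gives 82 per group without continuity correction and 91 with it. The stated 91 is reproduced, so the planned effect is ΔE = 0.40 − 0.20 = 0.20.

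**Inputs.**
- c: unit cost of one breath test. The documents give none, so it is an assumption, with EUR 100, 250 and 500 used as a range.
- r_I and r_C: share of parents in the intervention and usual-care arms whose questionnaires record the test, with at most one test counted per child. The documents give neither, so these are scenarios.
- ΔE = 0.20, from the sample-size section.

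**Formulas.**
- Incremental test cost as recorded: c × (r_I − r_C).
- Incremental test cost of the strategy: c, one test per intervention child and none for usual care.
- Shortfall per intervention child: c × [1 − (r_I − r_C)].
- Understatement of the health-care ratio: shortfall / ΔE.

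| r_I | r_C | Recorded | Shortfall | Ratio understated by | c = 100 / 250 / 500 (EUR) |
|---|---|---|---|---|---|
| 1 | 0 | c | 0 | 0 | 0 / 0 / 0 |
| 0.9 | 0.5 | 0.4c | 0.6c | 3c | 300 / 750 / 1,500 |
| 1 | 1 | 0 | c | 5c | 500 / 1,250 / 2,500 |
| 0.5 | 0.5 | 0 | c | 5c | 500 / 1,250 / 2,500 |
| 0 | 0 | 0 | c | 5c | 500 / 1,250 / 2,500 |

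The recorded cost equals c only in the first row, where every intervention parent and no usual-care parent reports the test. Because r_I cannot exceed 1 and r_C cannot fall below 0, the shortfall is never negative. Under these inputs the error can only favour the test.

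**Sensitivity to the effect.** If the true difference were 10 points, full loss would understate the ratio by c/0.10 = 10c (EUR 1,000, 2,500 and 5,000).

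**In money.** Full loss over 110 intervention children is 110c, or EUR 11,000, 27,500 and 55,000.

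**QALY ratio.** The shortfall in cost from the test is the same, but no QALY difference is planned, so the effect on that ratio cannot be sized.

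**The case against.** The strongest reply is that the plan never charges a test to usual care. It names the test as a cost item, defines the intervention as providing the diagnosis, and builds its curves around whether the test is cost-effective. All of this suggests that the test belongs to the intervention arm, and an analyst could charge it so. The article condenses a fuller plan, where arm attribution and prices may be set out. The questionnaire description is also a summary, and its item for other diagnostic procedures might capture the test.

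Much of this stands. A reader might infer that the test cost cancels exactly and that the ratio is certainly biased. The documents do not support that: cancellation needs equal reporting in the two arms. Only intervention parents receive the result during follow-up, so reporting may well differ. What does not fall away is that the article goes beyond silence. It states where the quantity of this item comes from, and that source gives the right answer in one extreme case only.

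Two further inferences are tempting and should not be drawn:
- **Baseline form.** Because it has a three-month recall, a reader might conclude that 15 months of cost are summed for year 1 and 27 months for two years. The article does not say that the baseline form is added to follow-up costs, and it fixes a 2-year horizon. Pre-randomisation use would in any case balance between arms in expectation.
- **Study visits.** A reader might add that protocol-mandated visits and lung function tests distort the comparison. They fall equally on both arms and do not bias the difference.

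The size is also open. No price is given, and the project aims at a cheaper point-of-care device. If the strategy both saves money and improves control, the ratio is negative and hard to read. The shortfall of up to c per child then appears as an overstated saving.

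**Conclusion.** The point holds in limited form. As written, the incremental cost of the breath test depends on differential parental reporting, so the intervention's own cost may be partly or wholly lost and the economic result made too favourable to the test. Full loss understates the health-care ratio by 5c at the planned 20-point difference: EUR 500 to 2,500 per additional controlled child for c between EUR 100 and 500. With 90% v 50% reporting the understatement is 3c.

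This rests on an assumed price, on reporting shares the documents do not give, on at most one test counted per child, and on the quantity rule being followed literally. The direction does not depend on the price. It should be corrected before the economic analysis, because test use and disclosure are known from the trial's own records and recall is not needed.

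**What to change.** In the economic section:

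1. Remove the breath test from the items obtained by questionnaire.
2. Charge one test to each child allocated to the intervention arm, counted from trial records and valued at the central laboratory's cost price.
3. Treat tests performed in usual care as research cost. Handle usual-care results released early under the safety rule in a sensitivity analysis, since charging them to usual care would itself lower the incremental cost.
4. Vary the unit price of the test in the sensitivity analysis.

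The cost is a few sentences and one cost price from the laboratory, with no new data from families. The ratio becomes less favourable to the test than under the present wording, by up to 5c at the planned effect.
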